#### Patient follow-up

Symptomatic response will be assessed through subjective patient report and completion of the UW-QoL and FACT-H&N questionnaires (Supplemental Material). Treatment-related toxicity during and after completion of PULSAR will be measured according to the CTCAE v5.0. Local tumor response will be assessed clinically and/or radiographically (e.g., by CT, PET, MRI), as applicable. Patient follow-up will be measured starting from the time of trial enrollment. Patient clinical assessments during PULSAR will occur within 7 days of each radiation treatment and consist of brief history, physical exam, and assessment of treatment-related toxicity. After receipt of the last PULSAR fraction, patients will be assessed clinically at 3 months +/- 28 days, 6 months +/- 28 days, 12 months +/- 28 days, 18 months +/- 28 days, and 24 months +/- 28 days post-treatment. These follow-up visits will consist of a history and physical exam, completion of the UW-QoL and FACT-H&N questionnaires, and measurement of toxicity. Surveillance imaging will be obtained per standard of care. Patients who experience disease progression will receive standard of care treatment(s) at the discretion of the treating physician. Patient enrollment, treatment, and follow-up is shown in Fig. 2.

**Fig. 2 Fig2:**
[figure not shown]
Trial Calendar. ^1^In primary diagnosis cases, pathologic confirmation is required. In recurrent and/or metastatic diagnosis cases, pathologic confirmation is not required if not beneficial to the patient as standard of care, and diagnosis can be assumed based on clinical and/or radiographic evidence. If available, Human Papillomavirus and/or p16 status will be collected and reviewed. ^2^Within 60 days of CT simulation. ^3^Questionnaires may be administered by telephone or electronically. ^4^May be repeated in between PULSAR fractions per treating physician’s discretion, as per section 6.5. ^5^During PULSAR course, toxicity assessments will occur within 7 days of each radiation fraction and may occur via telemedicine. ^6^May occur via telemedicine. ^7^For patients who undergo re-simulation and re-planning, an extended window of 14 +21/-10 days from most recent radiation therapy fraction to receive the next radiation therapy fraction to accommodate re-simulation scheduling and re-planning time. ^8^This will be the last follow-up for the safety lead-in portion, estimated to be at 12 months after trial opening. If proceeding to the phase II portion, the 15 patients in the safety lead-in portion will continue follow-up as per the study calendar, and all subsequently enrolled patients will follow the study calendar timeline and procedures. †Upon confirmation of eligibility and enrollment in the study, the following will be obtained prior to treatment (if not already performed)

### Adverse experience reporting and documentation

#### Adverse events

An adverse event (AE) is any untoward medical occurrence in a clinical investigation of a patient administered a pharmaceutical product and that does not necessarily have a causal relationship with the treatment. An AE is therefore any unfavorable and unintended sign (including an abnormal laboratory finding), symptom or disease temporally associated with the administration of an investigational product, whether or not related to that investigational product. An unexpected AE is one of a type not identified in nature, severity, or frequency in the current Investigator’s Brochure or of greater severity or frequency than expected based on the information in the Investigator’s Brochure.

The Investigator will probe, via discussion with the subject, for the occurrence of AEs during each subject visit and record the information in the site’s source documents. Adverse events will be recorded in the case report form (CRF). Adverse events will be described by duration (start and stop dates and times), severity, outcome, treatment and relation to study intervention, and the cause.

All adverse events should be treated appropriately. Such treatment may include changes in study intervention including possible interruption or discontinuation, starting or stopping concomitant treatments, changes in the frequency or nature of assessments, hospitalization, or any other medically required intervention. An assessment should be made at each visit (or more frequently, if necessary) of any changes in its severity, its suspected relationship to the study intervention, any of the interventions required to treat it, and its outcome.

#### AE evaluation

An investigator who is a qualified physician will evaluate all AEs. At each visit, the investigator will determine whether any AEs have occurred by evaluating the participant. Adverse events may be directly observed (through physical examination, laboratory test, or other assessments), reported spontaneously by the participant or by non-directive questioning of the participant at each study visit. The investigator must assess all AEs to determine:The severity grade according to CTCAE v5.0. If CTCAE grading does not exist for an adverse event, the severity of mild, moderate, severe, life-threatening and death (grades 1 - 5, respectively) will be used;Its relationship to the study intervention (related; probably-related; possibly-related; unlikely-related; not related);Its duration (start and end dates or if continuing at final exam);Action taken (none required; intervention not administered; dose reduced; dose delayed/interrupted; intervention discontinued);Treatment of adverse event (none required; medication given; procedure/surgery; other);Whether it constitutes a serious adverse event (SAE); and,Outcome (resolved; resolved with sequelae; persists, death; unknown).

The investigator’s assessment must be clearly documented in the study site’s source documentation with the investigator’s signature.

#### AE severity

The National Cancer Institute’s CTCAE v5.0 should be used to assess and grade AE severity, including laboratory abnormalities judged to be clinically significant. If the AE is not covered in the CTCAE, the guidelines shown in Table 1 below should be used to grade severity. It should be pointed out that the term “severe” is a measure of intensity and that a severe AE is not necessarily serious.

**Table 1 Tab1:** AE severity grading

Severity (Toxicity Grade)	Description
Mild (1)	Transient or mild discomfort; no limitation in activity; no medical intervention or therapy required. The subject may be aware of the sign or symptom but tolerates it reasonably well
Moderate (2)	Mild to moderate limitation in activity, no or minimal medical intervention/therapy required
Severe (3)	Marked limitation in activity, medical intervention/therapy required, hospitalizations possible
Life-threatening (4)	The subject is at risk of death due to the adverse experience as it occurred. This does not refer to an experience that hypothetically might have caused death if it were more severe

#### AE relationship to the study intervention

The relationship of an AE to the study intervention should be assessed by an investigator using the following guidelines in Table 2. The causality assessment must be made based on the available information and can be updated as new information becomes available.

**Table 2 Tab2:** AE relationship to study intervention

Relationship to intervention	Comment
Definitely	Previously known toxicity of the intervention; or an event that follows a reasonable temporal sequence from administration of the intervention; that follows a known or expected response pattern to the suspected intervention; that is confirmed by stopping or reducing the dosage of the intervention; and that is not explained by any other reasonable hypothesis
Probably	An event that follows a reasonable temporal sequence from administration of the intervention; that follows a known or expected response pattern to the suspected intervention; that is confirmed by stopping or reducing the dosage of the intervention; and that is unlikely to be explained by the known characteristics of the subject’s clinical state or by other interventions
Possibly	An event that follows a reasonable temporal sequence from administration of the intervention; that follows a known or expected response pattern to that suspected intervention; but that could readily have been produced by a number of other factors
Not Related/ Unlikely Related	An event that can be determined with certainty to have no relationship to the study intervention

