## Background

A significant proportion of patients with de novo or recurrent head and neck cancer (HNC) will not be candidates for standard of care definitive treatment(s) [1–3], which includes a combination of surgery, radiation therapy, and/or systemic therapy, and in some cases, standard of care stereotactic body radiotherapy (SBRT). Common contraindications for standard definitive treatment for HNC include locally advanced disease not amenable to definitive treatment because of the anticipated morbidity with primary or salvage treatment, poor performance status, presence of metastatic disease, or patient treatment preferences [4, 5]. In such cases, locoregional palliative radiation therapy is often utilized given the frequent accompanying symptoms of HNC such as pain or difficulty breathing or eating [6], with the most common HNC palliative radiation therapy regimens being the RTOG-8502 regimen (“quad-shot”) [7–9] and SBRT [10]. While these current palliative radiation therapy options can provide adequate symptom improvement, there are some limitations with these regimens as well.

With quad-shot, there are logistic challenges for both providers and patients given the twice-daily treatments, albeit for just two days total. Moreover, typically multiple cycles are needed to achieve maximal symptomatic benefit, although only about 50% of patients will be able to complete three or more cycles at which point the palliative response rate of this regimen is significantly increased [8, 11–13]. Additionally, while newer radiation therapy techniques such as intensity modulated radiation therapy (IMRT) have been employed to enhance the quad-shot regimen, it represents an older radiation therapy practice which may not fully leverage more recent advances in radiation therapy technology. Regarding SBRT, there is the possibility for severe toxicity, minimization of which is important in the palliative setting, as well as efficacy concerns, particularly for larger tumors or in the re-irradiation setting [6, 14–16]. However, a main limitation across all palliative radiation therapy regimens is suboptimal local control. Local tumor progression negatively impacts symptoms and possibly overall survival given the frequency at which locoregional tumor progression causes death in patients with HNC [17–19].

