## Methods/design

### Study design

This is a single-center (UCLA), single-arm, prospective phase II study with a safety lead-in. 43 subjects are planned. Each subject will receive the same PULSAR radiation therapy course as described below. The first 15 enrolled patients will be evaluated in the safety lead-in portion. If 5 or more of these 15 patients experience CTCAE v5.0 grade 3 or 4 or any patient experiences a grade 5 toxicity probably attributable to PULSAR during or within three months after completion of PULSAR, the study will be stopped for safety concerns; otherwise, the study will proceed, and those initial 15 patients will be included in the 43 subject sample. The trial schema is shown in Fig. 1.

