##### Secondary endpoints

Measurement of grade 3 or higher treatment-related toxicity during or within 24 months after completion of PULSAR, according to the CTCAE v5.0.Disease progression free survival (PFS), defined as the time from enrollment to the first objectively documented disease progression, either in or out of the treated field per radiographic and/or clinical evaluation, or death due to any cause. Participants who experience death or are lost to follow-up prior to 1 year will be assessed by their last radiographic/clinical evaluation.Overall survival (OS), defined as the time between enrollment and death of any cause. Participants who are lost to follow-up prior to 1 year will be censored at the date of their last documentation in the medical record system.Impact of PULSAR on symptoms/quality of life as measured by the UW-QoL and FACT-H&N validated questionnaires.Measurement of the frequency of re-simulation and/or adaptive planning required with PULSAR.Evaluation of the standard of care tumor and OAR dosimetry with PULSAR.Evaluation of the safety and efficacy of combination PULSAR and cancer-directed systemic therapy in enrolled patients receiving cancer-directed systemic therapy will be descriptive and exploratory.

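### In the causality table, a known radiation toxicity of uncertain cause fits both Definitely and Possibly, so one such grade 5 event can or cannot close the trial depending on the row chosen

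*Protocol article*

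**What the plan says.** Under the heading on AE relationship to the study intervention, causality "should be assessed by an investigator using the following guidelines in Table 2". The rows that matter are these:

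- **Definitely** begins "Previously known toxicity of the intervention; or an event that follows a reasonable temporal sequence from administration of the intervention". It then adds an expected response pattern, confirmation by withdrawing or lowering the dose, "and that is not explained by any other reasonable hypothesis".
- **Probably** asks for timing, pattern and the same dechallenge, and requires that the patient's clinical state or other interventions be unlikely explanations.
- **Possibly** asks for timing and an event "that follows a known or expected response pattern to that suspected intervention". Its last condition sets it apart from the rows above: "but that could readily have been produced by a number of other factors".

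The lead-in stop rule (Abstract, Study design, and Safety lead-in/interim analysis) has two limbs. One closes the trial when at least five of the first 15 patients reach grade 3-4. The other closes it when this is seen: "any patient experiences a grade 5 toxicity probably attributable to PULSAR during or within three months after completion of PULSAR".

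Two sources of competing causes are built into the trial. The Background section says that palliative radiotherapy is used "given the frequent accompanying symptoms of HNC such as pain or difficulty breathing or eating". The section on cancer-directed systemic therapy permits chemotherapy, targeted agents and immunotherapy during and after PULSAR.

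**The concern.** The strongest causality rating has the weakest entry condition. Its first alternative asks only that the toxicity be a known one. It sets no time relation and does not ask whether something else explains the event. The Possibly row describes an event with a known pattern and a ready alternative cause. The two rows therefore overlap, and the overlap skips the row between them.

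This matters because the stop rule draws its line between Possibly and Probably. An investigator who reads the table from the top can count an event toward closure. One who goes to the row that best describes the uncertainty will not count it. Both follow the table. In a palliative head and neck population, often on concurrent drugs, events of uncertain cause are to be expected.

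**Working it through.** The plan states no figure on this point, so there is none to reproduce. The check is a reading of the rows, followed by an illustration.

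**Step 1: the test event.** Take an event of a type known to follow radiation, with plausible timing, whose cause is uncertain because the tumour or a systemic agent could readily have produced it. That tumour symptoms such as pain or trouble eating are also radiation toxicities is an assumption, as the article lists no expected toxicities.

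**Step 2: apply each row of Table 2.**

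- Definitely, first alternative: asks only for a known toxicity. Met.
- Definitely, second alternative: fails on "and that is not explained by any other reasonable hypothesis".
- Probably: fails, because other causes are not unlikely.
- Possibly: timing met, pattern met, alternative cause met. Met.
- Not related or unlikely related: needs certainty that there is no relation. Fails.

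The event fits the first and third rows and not the second. The protocol gives no tie-break.

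**Step 3: the grade 5 limb of the stop rule.** Probable attribution plainly applies here. It is read as probable or stronger, the only sensible reading, though the text does not say so. One counted death closes the trial. Let q be the assumed chance that a lead-in patient has a dual-fit death within the window. Then

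P(at least one in 15) = 1 − (1 − q)^15

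- q = 1%: 1 − 0.99^15 = 0.140
- q = 2%: 1 − 0.98^15 = 0.261
- q = 5%: 1 − 0.95^15 = 0.537

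This is the chance that at least one such death arises. Unless the trial has to stop for another reason, the row chosen then decides closure.

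**Step 4: the grade 3-4 limb, only if attribution governs it too.** Let p be the share of patients with a counted event. Then P(stop) = P(X ≥ 5), with X binomial (15, p). Suppose 10% of patients have a clearly attributable event and a further 5%, 10% or 20% have only a dual-fit event (all assumed).

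- Dual-fit rated Possibly: p = 0.10, P(stop) = 0.013.
- Dual-fit rated Definitely: p = 0.15, 0.20 or 0.30, P(stop) = 0.062, 0.164 or 0.485.

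If attribution does not govern this limb, the shift through Table 2 is zero.

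**Step 5: what the first alternative currently does.** Probably and the second alternative of Definitely both require dechallenge. After the fifth fraction there is no dose left to withdraw or lower. Read literally, a toxicity that begins in the three months after completion can rise above Possibly only through the first alternative of Definitely. Deleting that alternative alone could leave post-treatment toxicity uncounted.

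**The case against.** The strongest reply is that the first alternative speaks of a toxicity of the intervention, not of any event type that radiation can produce. That stands in part. A reader might infer that a swallowing problem known to come from tumour growth would be rated Definitely by type. The text does not support this, since such an event is not a toxicity of PULSAR. The section on AE and SAE reporting also keeps disease progression itself out of the AE record, though events associated with it may be recorded. The uncertain case remains. There, whether the event is a toxicity of the intervention is the very question the table is meant to settle.

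Second, the table is guidance. A qualified physician judges each event, the rating can be updated, and the DSMB reviews each SAE monthly and weighs other causes. The Possibly row also describes the uncertain case more specifically. These safeguards soften the problem. None of them says which row prevails.

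Third, a reader might infer that the overlap sharply raises the chance of closure on the five-of-15 count. The documents do not establish that. In Study design and in Safety lead-in/interim analysis the attribution phrase follows the grade 5 clause, and its reach back to grade 3-4 is ambiguous. The size of any shift also rests on assumed rates and on every dual-fit event being rated Definitely.

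Fourth, a reader might carry the point over to the secondary endpoint, "Measurement of grade 3 or higher treatment-related toxicity during or within 24 months after completion of PULSAR". That section sets no probable-attribution cut. If events rated Possibly count as treatment-related, both rows count and the overlap changes nothing.

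**Conclusion.** The point holds in limited form. As written, Definitely and Possibly overlap for a known radiation toxicity of uncertain cause, with no precedence rule, and they fall on opposite sides of the stop rule's attribution line. The effect is clear for grade 5, where the rating of one death can decide closure. The illustrative chance of at least one such death in 15 is 14%, 26% or 54% at assumed rates of 1%, 2% or 5%. The grade 3-4 figures are conditional on a reading that the protocol leaves open. The wording defect depends on none of these rates. It rests on the literal structure of the Definitely row and on reading probable attribution as probable or stronger.

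**What to change.** Edit Table 2 and the matching case report form guidance together:

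1. Make known toxicity one way to meet the response-pattern element of Definitely. Require reasonable timing and the absence of another reasonable explanation (tumour, systemic therapy, comorbidity) in every case. An event that other factors could readily have produced then fits Possibly only.
2. In both Definitely and Probably, apply the dechallenge clause only where fractions remain to be given. Toxicity arising after the last fraction can then still be rated Probably or Definitely and count within the three-month window. This has to accompany the first change, for the reason in Step 5 of the working.
3. State in the stop rule that Probably and Definitely count, and reconcile the sections on whether attribution governs the grade 3-4 limb.

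The cost is a few lines of text. The small downside is that some events now rated Definitely by type alone will be rated lower.

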#### Safety lead-in/interim analysis

The study includes a safety lead-in portion, with formal evaluation on enrollment of the 15^th^ subject. The trial will be stopped if 5 or more patients in the safety lead-in portion experience a serious adverse event, defined as a CTCAE v5.0 grade 3 or 4 toxicity, or if any patient experiences a grade 5 toxicity probably attributable to the intervention during or within three months after completion of PULSAR.

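### The lead-in stop rule counts toxicity probably attributable to PULSAR, but the protocol's definition of that category cannot be met by events arising after the last fraction, and the rule does not say that more certain categories count

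*Protocol article*

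**What the plan says.** **The rule.** The Study design section of the protocol article sets the counts: "If 5 or more of these 15 patients experience CTCAE v5.0 grade 3 or 4 or any patient experiences a grade 5 toxicity probably attributable". The attribution there is to PULSAR, and the window covers treatment and the three months that follow it. The abstract gives the same rule. The section Safety lead-in/interim analysis restates it differently. There the trial stops if 5 or more lead-in patients "experience a serious adverse event, defined as a CTCAE v5.0 grade 3 or 4 toxicity, or if any patient experiences a grade 5 toxicity". In that restatement the attribution phrase and the same three-month window come only at the end of the sentence.

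**The attribution method.** The section AE relationship to the study intervention tells investigators to assess causality by the guidelines in Table 2.
- *Probably* is a list of conditions that must all hold. Among them is an event "that is confirmed by stopping or reducing the dosage of the intervention; and that is unlikely to be explained by the known characteristics". The row then refers to the patient's condition and to other treatments as competing explanations.
- *Definitely* opens with an alternative, that the toxicity is already known for the intervention. The word 'or' joins this to a list that contains the same stopping-or-reducing condition.
- *Possibly* requires that other factors could readily have produced the event.
- Not related and unlikely related share one row.

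**A second scale.** The AE evaluation section records "Its relationship to the study intervention (related; probably-related; possibly-related; unlikely-related; not related": five levels, with no *Definitely*.

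**Seriousness.** The AE severity section says that "a severe AE is not necessarily serious", and the Serious Adverse Event section defines seriousness by outcome, not by grade.

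**The concern.** A stop rule works only if the events it is meant to count can receive the label it counts. Here the label depends on seeing the event respond when the intervention is stopped or reduced. PULSAR is a finite course of five fractions, and the rule expressly extends three months beyond the last one. In that period the condition cannot be met.

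The next category up does not clearly repair this. A recognised late radiation toxicity may qualify as *Definitely*, but the rule as written does not name that category. A late event that is not already known, and that has no other ready explanation, fits none of the rows well.

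The restatement in the statistics section adds a separate ambiguity. A second 'if' splits the sentence, so the attribution phrase can be read as belonging to the grade 5 limb alone. On that reading, grade 3-4 events unrelated to PULSAR would count.

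The two readings err in opposite directions: one can miss attributable toxicity, the other can stop the trial on background events. The decision turns on the fifth event, or on a single death, so the count should not depend on which reading is taken.

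**Working it through.** The article states no operating characteristics for the stop rule, so there is no figure of the plan's own to reproduce. The check has three parts.

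**1. Which row can hold an event first arising after fraction five?**

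| Table 2 row | Can a late event qualify? | Named in the rule? |
|---|---|---|
| *Definitely* | Yes, if the toxicity is already known (the 'or' route). No by the other route, which needs stopping or reducing | No |
| *Probably* | No, because stopping or reducing is a required condition | Yes |
| *Possibly* | Only if other factors could readily explain it | No |
| *Not/unlikely related* | Not for an attributable event | No |

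The one category named in the rule is thus closed to late events. While fractions remain, stopping is possible (the PULSAR treatment section provides for early termination), so the gap concerns events after the course.

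**2. How much of the window lies after the course?** Five fractions have four intervals. Taking three months as 91 days, the post-course share is 91 / (course + 91).

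| Interval | Course (4 intervals) | Post-course share |
|---|---|---|
| 4 days (14 − 10) | 16 days | 91/107 = 85% |
| 14 days (nominal) | 56 days | 91/147 = 62% |
| 24 days (14 + 10) | 96 days | 91/187 = 49% |
| 35 days (14 + 21, re-planning at every interval) | 140 days | 91/231 = 39% |

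This is a share of time, not of events.

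**3. What could undercounting do?** Let p be the true rate of attributable grade 3-4 toxicity per patient, and s the share of affected patients whose event can be labelled so that it counts. Then P(stop) = P(X ≥ 5), with X binomial(15, p × s). The article gives neither p nor s; both are assumptions.

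| p | s = 1 | s = 0.5 | s = 0.25 |
|---|---|---|---|
| 20% | 0.16 | 0.01 | 0.001 |
| 30% | 0.48 | 0.06 | 0.004 |
| 40% | 0.78 | 0.16 | 0.01 |
| 50% | 0.94 | 0.31 | 0.03 |

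For the grade 5 limb, P(stop) = 1 − (1 − p × s)^15. At p = 5% this is 0.54 for s = 1, 0.32 for s = 0.5 and 0.17 for s = 0.25.

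On the opposite reading of the statistics section, unrelated grade 3-4 events count in full. The s = 1 column then applies to the background rate: an assumed 20% stops the trial with probability 0.16, and 30% with 0.48, without any PULSAR toxicity.

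**The case against.** - **Table 2 is guidance.** It is introduced as guidelines, and causality is to rest on the available information. Most investigators would read probably attributable as 'at least probably'; the rule does not cite Table 2 or use the label probably-related. This stands as a reason to expect a smaller effect in practice. It does not remove the conflict, because Table 2 is the protocol's stated attribution method and nowhere does the article say 'at least'.
- **Late events are not capped at *Possibly*.** A reader might infer that every toxicity after the fifth fraction drops to *Possibly*. Table 2 does not support that: the known-toxicity route into *Definitely* needs no stopping or reducing, and *Possibly* has its own condition. This stands. The gap is that the rule does not name *Definitely*.
- **Late events are not invisible.** All SAEs go to the DSMB whatever their relationship, deaths within 2 business days, and the DSMB reviews each SAE monthly. This stands and limits the harm, but it does not repair the numeric rule.
- **Attribution probably covers both limbs.** In the abstract and Study design, grade 3 or 4 shares its noun and modifiers with grade 5. In the statistics section, detaching attribution from grade 3-4 would detach the time window too, which is unlikely to be meant. This is the more natural reading, but the text should settle it.
- **The serious adverse event wording is a local definition.** "experience a serious adverse event, defined as a CTCAE v5.0 grade 3 or 4 toxicity" does not alter the threshold. It does conflict with the protocol's own use of the term elsewhere.

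**Conclusion.** The conflict holds on the text. The rule covers three months after the course, and the only category it names cannot be met by events first arising then. The more certain category is not named, two causality scales are in use, and the statistics section leaves the scope of attribution open.

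The size is uncertain. Between 39% and 85% of the window's time falls after the course, depending on the intervals. The fall from 0.78 to 0.16 at a 40% rate is an illustration that assumes half of the affected patients go uncounted.

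A reader might go further and conclude that the rule cannot see most of its window, with the chance of stopping at a 40% rate falling from 0.78 to about 0.07 (0.40 × 56/147 = 0.152, then P(X ≥ 5)). That requires that no post-course event counts, that events spread evenly over time, and that the course lasts exactly 56 days. The documents support none of these, and the route into *Definitely* together with the usual reading of 'probably' speaks against the first.

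Severity is moderate: a contradiction in the only numeric safety stop, cheap to remove, with DSMB review as a partial safeguard.

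**What to change.** Reconcile the abstract, Study design, AE evaluation, Table 2 and Safety lead-in/interim analysis:

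1. Use one list of causality categories in AE evaluation, Table 2 and the CRF.
2. Make the *Probably* and *Definitely* definitions usable after a completed course, with response to stopping or reducing considered only where fractions remain.
3. State that the rule counts events at least probably related to PULSAR, including the top category, whether it is called definitely or related.
4. Have the sponsor state whether attribution and the three-month window apply to both the grade 3-4 and the grade 5 limb, and use that one sentence wherever the rule appears.
5. Delete the phrase in the statistics section that defines grade 3-4 toxicity as a serious adverse event.

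The thresholds, the 15 lead-in patients and the visits stay as they are. The cost is wording in five places and the CRF category list. It should be done before lead-in events are classified for the stop decision.
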